## Abstract

**Background:**

Glaucoma is the leading cause of irreversible blindness worldwide, causing continuous and progressively worsening damage to visual function, which leads to vision loss. Optic nerve protection is an important treatment for glaucoma with controlled intraocular pressure (GPCI), but to date, there is no universally accepted effective optic nerve protection agent. Acupuncture can protect the optic nerve by increasing blood flow to the eye. However, fear of pain or the limitations of treatment place and time lead to poor patient compliance. Press-needle therapy is a characteristic of traditional Chinese medicine (TCM) external treatment methods; its safety is high, the effect is fast and lasting, it is easy to conduct, and it has high patient compliance.

**Objective:**

The objective of the trial is to evaluate the safety and clinical efficacy of press-needle therapy and investigate whether it can improve visual function by regulating eye blood circulation in patients with GPCI.

**Methods:**

In total, 192 participants aged 18-75 years with GPCI from the Mianyang Central Hospital, the Mianyang Hospital of Traditional Chinese Medicine, and the Mianyang Wanjiang Eye Hospital will participate in this study. Participants will be allocated to 2 treatment groups (experimental and control groups) in a ratio of 1:1 and will undergo press-needle therapy and sham press-needle therapy, respectively, for the same 4-week period. Primary outcomes will include the best-corrected visual acuity (BCVA), optical coherence tomography angiography (OCTA), color Doppler flow imaging (CDFI), and visual field assessment results. Secondary outcomes will include the intraocular pressure (IOP) and traditional Chinese medicine (TCM) clinical symptom scales. The primary outcomes and safety assessments will be measured at baseline and 4 weeks thereafter, while the secondary outcomes will be measured at baseline and 1, 2, 3, and 4 weeks thereafter.

**Results:**

Recruitment and data collection began in February 2023. The final outcomes are expected in September 2025. As of October 2024, the project had recruited 220 eligible participants, of whom 192 (87.3%) will complete the study, exceeding initial projections for the study time frame. The remainder of the participants will provide the ability to explore cross-level interactions that could not be statistically powered at the outset. The strengths of the project include rigorous data collection, good retention rates, and high compliance rates.

**Conclusions:**

This study will provide data on the effects of press-needle therapy on visual function and ocular circulation in patients with GPCI, and these results will help demonstrate whether acupuncture can improve patients’ visual function by regulating ocular circulation, thus providing a clinical and theoretical basis for the wider application of acupuncture therapy in GPCI.

**Trial Registration:**

Chinese Clinical Trial Registry ChiCTR2300067862；https://tinyurl.com/mrxd58x9

**International Registered Report Identifier (IRRID):**

DERR1-10.2196/67737

## Introduction

Glaucoma is a leading cause of irreversible blindness worldwide [1]. Progressive degeneration of retinal ganglion cells (RGCs) and the optic nerve is the basic pathological characteristic of glaucoma [2]. Optic nerve protection is the focus of glaucoma treatment based on intraocular pressure (IOP) control. Neuroprotective targets include glutamate-induced neurotoxicity, nitric oxidase synthetase, neurotropins, calcium channel receptors, free radicals, vascular insufficiency, and the rho-kinase pathway [3]. Nevertheless, at present, there is no satisfactory neuroprotective agent for glaucoma.

Ocular blood flow disorder is a potential cause of visual field deterioration in patients with glaucoma [4]. Therefore, therapeutic options to protect the optic nerve in glaucoma by improving ocular blood flow have attracted increasing attention [3]. Acupuncture therapy has been used to treat glaucoma for thousands of years and has demonstrated favorable safety and convenience [5]. Acupuncture can modify glaucoma blood flow parameters to protect the optic nerve, such as increasing the flow of blood in the eye [6] and reducing anomalies of blood flow in the central artery of the retina [7]. Acupuncture treatments relay electrical signals via the dorsal root ganglion (DRG) and spinal cord, finally regulating ocular blood flow [8].

However, the fear of acupuncture pain or the limitations of the treatment place and time lead to poor patient compliance. Press-needle acupuncture is one kind of acupuncture that has a longer treatment duration and simpler operation with less pain [9]. The theoretical basis of press-needle therapy is the combination of acupuncture theory and skin meridian and acupoint theory. *Suwen: Treatise on the Dermis* states that “all twelve meridians are also part of the skin” and that “the skin is closely related to the veins. The skin is also part of the pulse.” The dermis is connected with the 12 meridians by qi and blood. Through the 12 meridians, the 12 dermises are in close contact with the 5 viscera, 6 internal organs, and the eye orifices, forming a coordinated and unified organic whole. Press-needle therapy has been widely used to treat glaucoma with controlled intraocular pressure (GPCI), but useful empirical research is insufficient for its popularization and application. The disadvantages of less rigorous designs, small sample sizes, and low quality have led to many traditional Chinese medicine (TCM) studies being insufficient to convince people of its value.

Hence, a randomized, sham-controlled trial will be conducted to assess the potential of press-needle therapy in improving visual function and eye blood circulation in patients with GPCI.

## Methods

### Research Objectives

The main objectives of this study are twofold: (1) to observe the clinical efficacy of press-needle therapy in patients with GPCI and provide feasible and affordable press-needle treatment for them and (2) to investigate whether press-needle therapy improves the visual function of patients with GPCI by regulating eye blood circulation.

### Trial Design and Setting

This multicenter, sham-controlled, blinded, randomized trial of press-needle therapy (Seilini Ltd) for GPCI will be executed in the Mianyang Central Hospital (Sichuan, China), the Mianyang Hospital of Traditional Chinese Medicine (Sichuan, China), and the Mianyang Wanjiang Eye Hospital (Sichuan, China). The study time schedule is presented in Table S1 in Multimedia Appendix 1.

### Ethical Considerations

The trial protocol was approved by the Science and Technology Department of Sichuan Province (approval no: 2021YJ0443), the National Natural Science Foundation of China for the Youth (approval no: 82305324), Mianyang Central Hospital Incubation Subjects (approval no: 2020FH07), and the Medical Ethics Committee of the Mianyang Central Hospital (approval no: S2021046 (02)). It has been registered with an identifier (ChiCTR2300067862) with ClinicalTrials. The study will be strictly conducted according to the principles of the Declaration of Helsinki, as well as Good Clinical Practice (GCP) guidelines. The trial will be performed in accordance with the SPIRIT (Standard Protocol Items: Recommendations for Interventional Trials) checklist [10]. Signed informed consent will be obtained from all patients or their legal guardians by specific researchers prior to beginning the trial. If there are changes to the eligibility criteria, outcomes, or analyses, a new version of the protocol will be submitted to the Medical Ethics Committee of the Mianyang Central Hospital for approval.

### Participants and Recruitment Strategy

In total, 192 patients with GPCI recruited from the Mianyang Central Hospital, (Sichuan, China), the Mianyang Hospital of Traditional Chinese Medicine (Sichuan, China), and the Mianyang Wanjiang Eye Hospital (Sichuan, China) will participate in this study. All patients will be screened by specialists and acupuncturists according to the diagnostic criteria in the *European Glaucoma Society Terminology and Guidelines for Glaucoma* [11]. The TCM syndrome of kidney deficiency and blood stasis will be diagnosed based on guidelines delineated in the *Clinical Research Guideline of New Investigational Drugs in Traditional Chinese Medicine* [12].

### Inclusion and Exclusion Criteria

Participants who meet the following inclusion criteria will be eligible for the study:

Diagnosed with primary open-angle glaucoma (POAG) [13]: open anterior chamber angle, pathologically high intraocular pressure (HIOP), with a peak IOP exceeding 21 mmHg (1 mmHg=0.133 kPa) within a 24-hour period, indicative of glaucomatous neuropathy (retinal nerve fiber layer defect [RNFLD] or optic disc changes) or visual field loss or both. Other causes resulting in HIOP were excluded for this diagnosis. Note that only 1 eye from each patient will be selected for examination.Having a visual field defect that can be assessed through standard automated perimetry with a reliability factor of less than 15%, as well as an IOP below 18 mmHg, at least 3 months after undergoing antiglaucoma surgery.Exhibiting a Chinese syndrome pattern associated with kidney deficiency and blood stasis.Refraining from the use of any other optic nerve protective agents, except for methylcobalamin, for a minimum of 2 months.Having a spherical refractive error ranging between +3.00 and –6.00 diopters, a fundus clearly visible without the need for pupil dilation, and a BCVA equal to or greater than 0.3.Within the age bracket of 18-75 years.In a conscious state and capable of cooperating with the examination and treatment process.Displaying a willingness to actively participate in the study and provide informed consent.

Participants who have any of the following conditions will not be eligible to participate:

Poorly controlled IOP (≤7 mmHg or >18 mmHg), accompanied by a thin filtering cystic bleb or bleb leakage.Glaucoma that is not open-angle glaucoma.A Chinese syndrome pattern that does not meet the criteria of kidney deficiency and blood stasis.Other conditions, such as macular degeneration, cataract, proliferative diabetic retinopathy, retinal vascular occlusion, or any other diseases that may cause visual field loss.Pregnancy or lactation.Abnormal primary liver or kidney function or serious systemic conditions, such as heart disease, primary hypertension, diabetes mellitus, or peptic ulcer disease.A history of allergic reactions to the ingredients of press-needle therapy or mecobalamin tablets.

### TCM Syndrome Differentiation

The TCM syndrome of kidney deficiency and blood stasis will be based on guidelines delineated in the *Clinical Research Guideline of New Investigational Drugs in Traditional Chinese Medicine* [12]: primary signs and symptoms include blurry visual acuity, narrow visual field, and eye distension, while secondary signs and symptoms include dry eye, limp aching lumbus, and knees.

The conditions for a diagnosis of kidney deficiency and blood stasis are the presence of at least 2 or more primary signs/symptoms and at least 2 or more secondary signs/symptoms. The necessary condition is a dark-purple tongue and a thready deep, stringy, or unsmooth pulse. The investigators must receive training in standard operating procedures (SOPs) for examining TCM symptoms. They will then conduct a symptom assessment survey using the TCM Symptom Score Scale (Figure 1) for each participant.

**Figure 1 figure1:**
[figure not shown]
TCM Symptom Score Scale. TCM: traditional Chinese medicine.

### Recruitment Procedure

Potential participants with GPCI were recruited from the Mianyang Central Hospital (Sichuan, China), the Mianyang Hospital of Traditional Chinese Medicine (Sichuan, China), and the Mianyang Wanjiang Eye Hospital (Sichuan, China). We used the internet, hospital announcements, and posters to provide a hotline calling for potential volunteers. If patients were interested in our study, researchers informed them in detail of the purpose and content of the research and the benefits and risks of participating.

After screening, participants meeting the inclusion criteria will be enrolled. Frequent follow-up phone calls are an important aspect of adherence monitoring. Every participant will have the right to withdraw from the trial at any time. Furthermore, it will be obligatory for all subjects to sign an informed consent document prior to commencement of the trial.

### Randomization and Allocation

Baseline evaluation will be conducted for eligible subjects. All eligible patients will be stratified according to early, moderate, and advanced stages of glaucoma [14]. Patients with early glaucoma exhibit early glaucomatous visual field impairment, as characterized by a mean deviation (MD) of >–6 dB. Conversely, patients with moderate glaucoma present a moderate glaucomatous visual field loss, defined as MD≤–6 to ≥–12 dB. Patients with advanced glaucoma experience advanced glaucomatous visual field loss, defined as MD<–12 dB. SAS software will be used to automatically generate a set of random numbers ranging from 001 to 192. These numbers will be further classified into 3 ranges based on the disease stage. The early stage will incorporate random numbers from 001 to 064, the moderate stage will encompass numbers from 065 to 128, and the advanced stage will comprise numbers from 129 to 192. Following stratification, the participants will be assigned randomly to either an experimental group or a control group in a 1:1 ratio. Random numbers will be inserted into identical envelopes of equal dimensions, which will then be sealed to ensure concealment of group allocation and minimize the risk of selection bias. The random sequence allocation will be preserved and withheld from the investigators, statisticians, and outcome assessors to avoid detection bias.

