### Statistical Analysis

Statistical analysis will be conducted independently by statisticians. The data will be presented as means (SDs). IBM SPSS 22.0 statistical software will be used. All statistical tests will be 2-sided tests, and the limit for statistical significance will be set at *P*<.05. The chi-square test will be performed for categorical variables, the independent Student *t* test will be used for measurement data, and the rank-sum test will be used for grade data. To evaluate the covariate balance, baseline characteristics will be summarized and compared between the experimental group and the control group using simple descriptive statistics.

Due to the expected low number of missing data, we will deal with missing data by transferring the last data item to the final dataset. This participant's data will be invalidated in the full analysis set (FAS), and this case will not be included in the per protocol set (PPS). Finally, the statistical significance of the FAS and PPS will be analyzed. A consistent statistical significance will indicate a significant difference.

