## Results

The study flowchart is shown in Figure 2. The figure also presents an outline of the case distribution across each center, as well as comprehensive outline of precise measurements and designated data collection time points. Recruitment was conducted from February 2023 to March 2024. The first participant was enrolled in February 2023. As of October 2024, the project had recruited 220 eligible participants. At the time of submission, there were 192 (87.3%) participants, who will complete the study. The recruitment process is expected to continue until September 2025. The data will be further processed and analyzed in October 2025.

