This study is designed as a double-blind, placebo-controlled trial. To guarantee the quality of the study, its design and execution will be strictly performed with proper quality control. A training session for each center will be held to explain the detailed study protocol, the diagnosis of the TCM syndrome pattern, and the SOPs. The same investigator will be responsible for the examination of each patient at different times. All indicators will be assessed by independent assessors. The principal investigators, statisticians, and outcome assessors will be blinded to the treatment assignments until the database is locked.

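### Allocation is stratified by stage only and the stated tests are unadjusted, so between-hospital variation in 4-week change stays in the error: a modest loss of precision, not bias

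*Protocol article*

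**What the plan says.** Under Trial Design and Setting the article describes three sites: "This multicenter, sham-controlled, blinded, randomized trial of press-needle therapy", run at a central hospital, a hospital of traditional Chinese medicine and an eye hospital.

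Under Randomization and Allocation, stage is the only stratum: "All eligible patients will be stratified according to early, moderate, and advanced stages of glaucoma". One list serves the whole trial: "SAS software will be used to automatically generate a set of random numbers ranging from 001 to 192". It is divided by stage alone: "These numbers will be further classified into 3 ranges based on the disease stage", giving 64 numbers to each stage. Allocation is 1:1. No list or block per hospital is described.

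Under Statistical Analysis, categorical variables get a chi-square test. For continuous and graded outcomes the article names the independent Student t and the rank-sum test: "test will be used for measurement data, and the rank-sum test will be used for grade data". Baseline balance is examined descriptively. No model is named, and so no term for hospital or stage.

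Three statements bear on how much hospitals could differ. The Discussion says "The same investigator will be responsible for the examination of each patient at different times". Quality Control provides common training with a proficiency assessment, and the Discussion adds a training session at each centre. The Results say that the flowchart, which is not shown here, gives an "outline of the case distribution across each center".

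**The concern.** Doppler velocities, OCTA densities and symptom scores are obtained by staff, and the press needles are applied by acupuncturists for whom only a minimum experience is set. With three hospitals, the average 4-week change may differ between sites for reasons unrelated to arm, such as case mix, delivery of treatment or measurement variability.

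A list divided by stage balances the arms within stage but leaves the split within each hospital to chance. An unadjusted comparison then carries the between-hospital variation in its standard error. In a trial where one hospital happens to be unevenly split, the estimate also moves with that hospital's mean change. At stake are some precision and a ready answer to the question whether one hospital drives the result.

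**Working it through.** The article gives no figure for hospital variation, so there is none to reproduce. Its sample-size calculation compares two effective rates and does not enter here.

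**Inputs from the article:** three hospitals; 192 numbers, 64 per stage; 1:1 allocation, so 96 per arm; unadjusted tests at two-sided 0.05.
**Assumed:** 64 patients in each hospital; hospital's share *s* of the variance of change equal to 5%, 10% or 20%.

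**1. What cancels.** Suppose an examiner or hospital reads a constant amount *b* too high at both visits. Then change = (week 4 + *b*) − (baseline + *b*), and *b* drops out. Change is the stated form for visual acuity, visual field, IOP and symptoms. For OCTA and Doppler the article gives only the measurement times, and I read these as change too. What remains is variation between hospitals in the 4-week change itself.

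**2. Chance imbalance.** With 64 of 192 patients in a hospital and 96 of 192 on press needles, the number on press needles there is hypergeometric (stage strata ignored):

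SD = √[64 × 0.5 × 0.5 × (192 − 64)/(192 − 1)] = √10.72 = 3.27; 95% range 26 to 38.

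At the edge of that range (38 versus 26), if this hospital's mean change differs from the others' by *D*, the unadjusted arm difference shifts by (38 − 26)/96 × *D* = 0.125 *D*. The direction is random, so the average shift is zero.

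**3. Precision.** Removing the hospital share multiplies the standard error by about √(1 − *s*). The equivalent sample is 192/(1 − *s*).

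| *s* (assumed) | SE ratio | SE narrower by | 192 act like |
|---|---|---|---|
| 5% | 0.975 | 2.5% | 202 |
| 10% | 0.949 | 5.1% | 213 |
| 20% | 0.894 | 10.6% | 240 |

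Steps 2 and 3 describe one effect, not two. Chance imbalance is the route by which hospital variation reaches the error of the arm difference.

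**4. Validity and power by simulation.** Allocation was fixed at 32:32 in each stage, with hospital left free and equal expected hospital sizes. The effect was set to give 90% power unadjusted: (1.96 + 1.282) × √(2/96) = 0.468 SD. There were 6,000 replicates, so the Monte Carlo SE of a 5% rate is √(0.05 × 0.95/6000) = 0.3 percentage points.

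| *s* | Type I error, t test | Type I error, hospital in model | Power, t test | Power, hospital in model |
|---|---|---|---|---|
| 0% | 4.8% | 4.8% | 90.3% | 90.0% |
| 5% | 5.0% | 4.5% | 90.1% | 90.7% |
| 10% | 4.9% | 4.7% | 89.7% | 91.8% |
| 20% | 5.1% | 4.6% | 89.7% | 95.1% |

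The t test holds its level throughout. The gain in power is under one point at 5% and about five points at 20%. If hospital explains nothing, adjustment costs almost nothing.

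**The case against.** The strongest reply is that nothing here is invalid. The unadjusted test keeps its level, and the gain is small unless hospital explains a large part of the variance of change. That stands, and it sets the weight of the point.

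A second reply is that covariates belong in a statistical analysis plan, which may exist. In part this stands: such a plan could add hospital, and its absence from a condensed article would not by itself be a fault. But the article names the tests, and those tests have no place for hospital. A plan that adjusts would depart from what is published.

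Third, the mitigations are real. The same investigator sees a patient at each visit, which helps constant offsets cancel, and common training should narrow differences between sites. Neither balances the arms within a hospital nor removes variation in 4-week change.

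Three stronger readings are tempting and are not supported:

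- *The treatment effect is biased or the error rate inflated.* Allocation does not depend on hospital, and the simulation shows about 5%.
- *Examiner, machine or acupuncturist is confounded with hospital.* The article does not say so. It fixes the investigator within a patient and a minimum experience for acupuncturists, and it names one perimeter and one tonometer model. Differences by site are an inference.
- *The allocation should be re-blocked by hospital.* The Results report 220 recruited by October 2024 against a list of 192 numbers. They also say recruitment will continue to September 2025, but re-blocking could not rebalance allocations already made.

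**Conclusion.** The point holds as a modest loss of precision. Hospital is absent from both the stratification and the stated tests, so between-hospital variation in 4-week change stays in the error, and a chance imbalance in a given hospital goes uncorrected. The gain from adjustment is about 2.5%, 5% or 11% in the standard error if hospital explains 5%, 10% or 20% of the variance of change.

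Those shares and the equal hospital sizes are assumptions. The upper share may be generous once constant offsets have cancelled. It is worth changing because the change is cheap and can be fixed in advance, not because the stated analysis would mislead.

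**What to change.** Before database lock, state that for continuous outcomes the arm difference will be estimated from a linear model with arm, hospital (three levels, fixed), stage and the baseline value, in place of the independent t test. Add a descriptive display of the arm difference with its confidence interval in each hospital, without a test of significance.

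Hospital uses two degrees of freedom: residual 192 − 4 = 188 instead of 190 with arm and hospital alone. Stage takes two more and the baseline value one. No new data are needed, since the case distribution by centre is already reported. The Ethical Considerations section sends changes in analyses to the ethics committee as a new protocol version, so the cost also includes that submission. Analysis is planned for October 2025, and the model should be fixed while the analysts are still blinded. The allocation scheme can stay as it is.
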